#### Construction of the network

The template of the neuroimaging research laboratory of Stanford University (Functional Imaging in Neuropsychiatric Disorders Lab website; http://findlab.stanford.edu/functional_ROIs.html) will be used to explore the DMN and SN (54). For the ROIs of the DMN and SN, see Supplementary Tables S1, S2.

We will use the Brain Connectivity Toolbox to extract the connection information between various brain regions and draw the connection diagram at the macro level. This will be used to quantitatively describe the structure, function, connection model and topological characteristics of the human brain network. We will mainly focus on the brain regions related to PUs: the insula, ACC, supplementary motor area (SMA) and prefrontal cortex. We will take the DMN and SN as the main brain function networks to consider.

Degree, global efficiency, local efficiency, path lengths and cluster coefficients will be used to investigate the relationships between the changes in these two brain functional networks and the improvements in tics and PUs and to clarify the possible brain mechanisms underlying the effects of MHRT from the perspective of brain functional networks. We will assess global network integration, segregation and connectivity between modules using the following measures for the DMN and SN: (1) degree: number of edges connected to a node; (2) global efficiency: global transmission capacity of the network; (3) cluster coefficient: degree of network collectivization; (4) local efficiency: nodal connections to within-network nodes; (5) path length: optimal path from one node to another. To assess the reliability of the results and enhance comparability with previous research, exploratory analyses on the absolute Fisher r-to-z transformed Pearson correlation connectivity matrices will be performed using the same graph indices. The calculation formulas for these parameters are presented in Supplementary Figure S2.

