For the analysis of global graph measures, we consider a significance level of α = 0.05 significant. To correct for multiple comparisons in subnetwork analyses, we will use a D/AP-Sidak adjustment that considers the mutual correlation between outcome measures (https://www.quantitativeskills.com/sisa/calculations/bonhlp.htm). For between-network connectivity analyses, we will compute an α corrected for three comparisons, i.e., adjusted for the correlation (*r* = 0.544) between the three indices after training (αBN = 0.031). For subnetwork graph analyses, we will compute a separate α for each graph measure adjusted for the correlation between the respective subnetwork measures at baseline (rFPN = 0.387, αFPN = 0.026; rDMN = 0.408, αDMN = 0.026; rSN = 0.413, αSN = 0.027).

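### The pre-set imaging significance thresholds do not fit this trial: they assume three comparisons, include an unstudied FPN, and rest on correlations the trial cannot yet have

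*Protocol article*

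**What the plan says.** The Construction of the network section limits the imaging work to two networks: "We will take the DMN and SN as the main brain function networks to consider". Regions of interest are given for those two only, and the Introduction says the same. Five graph measures are planned: "Degree, global efficiency, local efficiency, path lengths and cluster coefficients will be used to investigate the relationships". The Statistical analysis section plans connectivity between DMN and SN, which is one pair.

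That section then sets the correction for multiplicity: "we will use a D/AP-Sidak adjustment that considers the mutual correlation between outcome measures". For between-network connectivity it says "we will compute an α corrected for three comparisons", using a correlation of 0.544 among three indices measured after training, with a resulting threshold of 0.031. For the subnetwork graph analyses it promises a separate threshold for each graph measure, based on baseline correlations, and prints "rFPN = 0.387, αFPN = 0.026; rDMN = 0.408, αDMN = 0.026; rSN = 0.413, αSN = 0.027".

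**The concern.** Four things do not fit together.

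- **An extra network.** FPN has a correlation and a threshold but no definition, no regions of interest and no other mention in the article. The Introduction names a central executive network, but only as background.
- **The comparison count.** Two networks form one pair, not three.
- **The correlations.** They are printed to three decimals, one of them from after training, in a document that describes recruitment (May 2022 to December 2023) and scanning as planned work. The only pilot figure reported is an effect size of 0.68 on the YGTSS. No imaging pilot is described.
- **The unit of correction.** The text promises one threshold per graph measure but prints one per network, so a reader cannot tell which tests form a family.

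The network parameters are the stated secondary outcomes, so these thresholds decide which mechanism findings for MHRT are called significant. If the family is settled only after the imaging results are known, the threshold can be chosen to suit them.

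**Working it through.** **Inputs.** From the Statistical analysis section: unadjusted α = 0.05; r = 0.544 (between-network), 0.387 (FPN), 0.408 (DMN), 0.413 (SN); stated thresholds 0.031, 0.026, 0.026, 0.027. The number of comparisons k is stated as three for the between-network threshold only. For the subnetwork thresholds it is not stated and has to be inferred.

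**Formula (D/AP-Sidak).** α_adj = 1 − (1 − 0.05)^(1/k^(1−r)).

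**Step 1: reproduce the plan.** For the between-network threshold with k = 3: 3^(1−0.544) = 3^0.456 = 1.650; 1/1.650 = 0.606; 1 − 0.95^0.606 = 0.0306, which rounds to 0.031. The same calculation for every entry:

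| Entry | r | Stated | k = 2 | k = 3 | k = 5 |
|---|---|---|---|---|---|
| Between-network | 0.544 | 0.031 | 0.0367 | **0.0306** | 0.0243 |
| FPN | 0.387 | 0.026 | 0.0330 | **0.0258** | 0.0189 |
| DMN | 0.408 | 0.026 | 0.0335 | **0.0264** | 0.0196 |
| SN | 0.413 | 0.027 | 0.0336 | **0.0266** | 0.0197 |

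Only k = 3 matches all four (k = 1 and k = 4 also fail). The arithmetic is sound; the inputs do not belong to this design.

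**Step 2: between-network test.** DMN and SN form one pair, so k = 1. Then k^(1−r) = 1 for any r, and α_adj = 0.05, not 0.031.

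**Step 3: subnetwork tests.** Two families are possible. Family-wise error is computed for equicorrelated two-sided normal tests at the printed r.

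| Family | Formula gives (DMN / SN) | Stated | Family-wise error at the stated threshold |
|---|---|---|---|
| Two networks, per graph measure (k = 2) | 0.0335 / 0.0336 | 0.026 / 0.027 | 4.9% / 5.1% |
| Five measures, within one network (k = 5) | 0.0196 / 0.0197 | 0.026 / 0.027 | about 11% for each |

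Under the first family the printed thresholds are stricter than the plan's own rule. Under the second they are more lenient.

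**Step 4: sensitivity to r.** The trial's own r is unknown. For r from 0 to 0.8 the formula gives 0.0253 to 0.0437 with k = 2, and 0.0102 to 0.0365 with k = 5.

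**Step 5: the formula itself.** D/AP-Sidak is approximate. With two tests at r = 0.41, using its own threshold of about 0.0335, family-wise error is about 6.3%, not 5%.

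**The case against.** The strongest reply is that these thresholds do not clearly inflate false positives. A separate threshold for each graph measure reads most naturally as a correction across subnetworks within each measure, which is k = 2. On that reading 0.026/0.027 holds about 5% family-wise error, and 0.031 for a single DMN-SN test is stricter than needed. The cost is then lost power. The text also says the thresholds will be computed, so the printed values could be replaced without changing the method, and the imaging outcomes are secondary.

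Much of this stands. A reader might infer from the five graph measures that the subnetwork thresholds are simply too lenient. The document does not support that as a general statement: it never declares the five measures to be one family, and the 11% arises only if they are. A reader might also infer that the values were carried over from a three-network study. Three networks would explain both the FPN entry and the three pairs, but the document gives no source, and an unreported imaging pilot cannot be excluded.

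The three indices could be read as within-DMN, within-SN and DMN-SN. The text, however, calls the analysis between-network, and that reading leaves the FPN entry unexplained.

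None of this makes the printed values usable. A pilot would not supply this trial's correlations, and about 5% error under k = 2 is a coincidence of a wrong count, since the plan's own rule gives about 0.034 there.

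**Conclusion.** The concern holds as a mismatch between the printed thresholds and the trial's design. It is not a demonstrated inflation of error.

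- **Certain from the document:** the FPN entry has no place in a DMN and SN study; three comparisons do not match one pair; and the after-training correlation cannot be this trial's own data in a plan that describes the trial as still to be run.
- **Inferred:** k = 3 for the subnetwork thresholds, because of the counts tried it alone reproduces them all.
- **Size:** the DMN-SN test is held to 0.031 instead of 0.05. The subnetwork thresholds of 0.026/0.027 compare with about 0.034 (two networks) or about 0.020 (five measures). These subnetwork figures are conditional on the printed r, and the error rates also on equicorrelated normal tests.

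Severity: should be fixed. The thresholds govern secondary outcomes only; the YGTSS analysis is unaffected.

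**What to change.** 1. Delete the FPN entry and all pre-filled correlations and thresholds.
2. Test the one DMN-SN connectivity index at 0.05.
3. Before imaging data are analysed, declare the subnetwork family: DMN and SN, and whether the five graph measures are corrected together or each measure separately. Make the promised unit (per measure) and the reported unit (per network) agree.
4. Control that family in one of two ways. Holm needs no correlation and holds the family-wise error rate. The alternative is the plan's formula with the true number of comparisons and correlations from the trial's own baseline data, with a note that D/AP-Sidak is only approximate.

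The cost is a change of analysis wording. Subnetwork thresholds may become somewhat stricter: Holm's first step is 0.05/2 = 0.025 for two tests and 0.05/5 = 0.010 for five, against the printed 0.026/0.027.

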Some theoretical understandings of the brain mechanisms involved in mindfulness take their lead from considerations about the roles of the major brain networks and their interplay (21). Functional connectivity in intrinsic brain networks, which include the salience network (SN), default mode network (DMN) and central executive network (CEN), has been suggested to be important in the networks prominently involved in cognition and mindfulness (26, 27). Mindfulness training involves participants training the attention system to inhibit irrelevant sensory stimuli and enhance relevant sensory stimuli (28) and consists of focusing attention on physical sensations (29). This suggests that mindfulness can improve the patient's perception of PUs. Mindfulness-mediated decreased connectivity between the cuneus and SN may be related to self-awareness (27). The primary node of the SN is within the anterior insular cortex (30). Neuroimaging studies have suggested that PUs are associated with the insula and anterior cingulate cortex (ACC) (31, 32). A review indicated that mindfulness-based treatments may be effective in restoring connectivity between the DMN and the CEN and SN in individuals with PTSD (33). Meditation practitioners showed significantly stronger connectivity between the DMN and SN (34), as well as increased connectivity in systems important for emotion and reward (35). This may explain why mindfulness reduces anxiety and depression and enhances wellbeing. On the other hand, TS patients exhibited a reduction in serial information transfer within the DMN and SN (36). TD patients benefit from increased functional connectivity within the DMN as a compensatory function (37). From the perspective of brain networks, we speculate that mindfulness can provide useful support for conventional HRT in TS patients. To understand the underlying mechanisms of mindfulness in TS, we will focus on two key brain networks, the DMN and SN.

Therefore, this project plans to carry out an RCT of MHRT in the treatment of TS, further systematically verify its efficacy and explore the brain mechanisms underlying the synergy of MHRT. The significance and value of this study are to form a suitable psychological and behavioral intervention scheme for TS, resolve the dilemmas in clinical treatment to a certain extent, and provide data for further clarifying the pathophysiological mechanisms underlying TS.

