## Methods/design

### Participants

#### Recruitment of participants

Recruitment of TS patients will be from the Department of Psychiatry, Beijing Children's Hospital, where participants will have received a diagnosis of TS from an experienced multidisciplinary team including at least two attending psychiatrists using the diagnostic criteria in the DSM-5. The inclusion criteria were as follows: (1) 7–12 years old; (2) Chinese children's Wechsler intelligence test IQ ≥ 80; (3) first onset with no previous treatment; and (4) right-handed. The exclusion criteria were as follows: (1) diagnosed with other mental disorders, apart from obsessive–compulsive disorder (OCD) or attention deficit hyperactivity disorder (ADHD); (2) diagnosed with epilepsy or other neurological diseases (including craniocerebral trauma); (3) claustrophobia; and (4) metallic foreign objects in the body. The recruitment period was predefined for one and a half years (May 2022 to Dec 2023).

Recruitment of healthy controls will be from a primary school in Beijing. The inclusion criteria were as follows: (1) aged 7–12 years; (2) IQ ≥ 80; and (3) right-handed. The exclusion criteria were as follows: (1) diagnosed with neurological or mental diseases; (2) claustrophobia; and (3) metallic foreign objects in the body.

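### The printed imaging significance thresholds are computed for three comparisons and include an undefined FPN, but the trial defines two networks, the DMN and SN

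*Protocol article*

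**What the plan says.** The Introduction narrows the imaging aim: "we will focus on two key brain networks, the DMN and SN". The section Construction of the network repeats this ("We will take the DMN and SN as the main brain function networks to consider"), points to ROI tables for those two networks only, and lists five graph indices for them: "Degree, global efficiency, local efficiency, path lengths and cluster coefficients will be used". The Statistical analysis section plans one between-network quantity, the connectivity between DMN and SN.

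The correction paragraph at the end of Statistical analysis sets the thresholds:

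- Global graph measures are not corrected: "For the analysis of global graph measures, we consider a significance level of α = 0.05 significant".
- For subnetwork analyses, "we will use a D/AP-Sidak adjustment that considers the mutual correlation between outcome measures".
- Between-network connectivity is corrected for three comparisons, using r = 0.544 "between the three indices after training", which gives 0.031.
- Subnetwork graph analyses are to have a distinct threshold per graph measure, based on baseline correlations, but the values printed are one per network: "rFPN = 0.387, αFPN = 0.026; rDMN = 0.408, αDMN = 0.026; rSN = 0.413, αSN = 0.027".

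**The concern.** A printed threshold is a decision rule, and these do not match the design described a page earlier. Three things stand out. The paragraph carries an FPN that has no definition and no ROIs. It counts three between-network comparisons where two networks allow one. It also quotes correlations to three decimals, one of them from after training, in a protocol that describes its scans as still to come.

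At stake is which network results are called significant. These are the trial's secondary outcome and its whole mechanism aim. An analyst who follows the paragraph literally would use a wrong cut-off for DMN–SN connectivity. For the graph measures, the analyst would have to choose the family after the fact.

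**Working it through.** **Inputs, all from the correction paragraph.** Overall α = 0.05. Correlations are 0.544 (between-network), 0.387 (FPN), 0.408 (DMN) and 0.413 (SN). Printed thresholds are 0.031, 0.026, 0.026 and 0.027.

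**Formula.** D/AP-Sidak for K tests with mean correlation r: α′ = 1 − (1 − 0.05)^(1/K^(1−r)).

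**Step 1: reproduce the printed values.** With K = 3:

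- Between-network: 3^0.456 = 1.650, so α′ = 1 − 0.95^(1/1.650) = 0.0306, printed as 0.031.
- FPN: 3^0.613 = 1.961, so α′ = 0.0258, printed as 0.026.
- DMN: 3^0.592 = 1.916, so α′ = 0.0264, printed as 0.026.
- SN: 3^0.587 = 1.906, so α′ = 0.0266, printed as 0.027.

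All four match, so the arithmetic is right for K = 3. Other counts do not match:

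| Family size | Between-network | FPN | DMN | SN |
|---|---|---|---|---|
| K = 2 | 0.037 | 0.033 | 0.033 | 0.034 |
| K = 3 | 0.031 | 0.026 | 0.026 | 0.027 |
| K = 5 | 0.024 | 0.019 | 0.020 | 0.020 |
| Printed | 0.031 | 0.026 | 0.026 | 0.027 |

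**Step 2: count what this trial has.** Two networks give C(2,2) = 1 pair. Three networks (FPN, DMN, SN) would give C(3,2) = 3 pairs, which is the count the paragraph uses.

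**Step 3: apply the plan's own rule to the trial's counts.** The printed r is kept only for illustration.

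- DMN–SN connectivity, K = 1: α′ = 0.05 whatever r is, against 0.031 printed.
- DMN and SN within one graph measure, K = 2: DMN 1 − 0.95^(1/1.507) = 0.0335 and SN 1 − 0.95^(1/1.502) = 0.0336, against 0.026 and 0.027 printed. The printed values are stricter than the rule requires.
- Five graph measures within one network, K = 5: DMN 1 − 0.95^(1/2.593) = 0.0196 and SN 1 − 0.95^(1/2.572) = 0.0197. The printed values are looser than the rule requires.

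**Step 4: allow for the unknown r.** The trial's own correlations are not known. For an assumed r between 0 and 0.8, K = 2 gives 0.0253 to 0.0437 and K = 5 gives 0.0102 to 0.0365. The printed subnetwork values cannot be carried over without both K and r.

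**Step 5: source of the correlations.** The MRI sections describe acquisition and processing in the future tense. The pilot in Sample size estimation is tied only to the YGTSS effect size, and the pilot data in the Discussion are tied to a prediction about tic severity. No imaging source is given. Three of the correlations are described as baseline values. Only the between-network one is described as after-training, so only the 0.031 threshold would depend on data from the outcome period.

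**The case against.** **A third network is not strictly excluded.** The Introduction mentions a central executive network as background, and the methods call the DMN and SN the main networks, not the only ones. That is fair. But no third network is selected, given ROIs or linked to the label FPN, so a reader cannot carry out an FPN test from this document.

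**Three could be a count of graph measures.** If some of the five indices fall under the uncorrected rule for global measures, three might remain for the subnetworks. The text makes no such split and lists all five for the DMN and SN. This reading would in any case not rescue the FPN entry or the three between-network comparisons.

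**A reader might infer that the thresholds inflate false positives.** That is not established. With two equicorrelated normal test statistics (r = 0.41, assumed), testing each at 0.026 gives a family-wise error of 4.9%. Five tests would give about 10.8%, but the plan does not say that the five measures form one family. Part of that figure also belongs to the formula: D/AP with K = 5 still gives about 8.4%. Whether D/AP controls error well is a separate question. A ten-test family of five measures in two networks would be a new choice, not a correction of this plan.

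**A reader might infer that the values were taken from another study, or from this trial's outcome data.** Neither can be shown. The article dates recruitment ("The recruitment period was predefined for one and a half years (May 2022 to Dec 2023") but does not say that any scan had been analysed. What stands is that the source is not stated.

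**The text says the thresholds will be computed.** They could therefore be recomputed under the stated rule. This lowers the severity, but it does not remove the printed numbers or the wrong count.

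**Conclusion.** The point holds in this form: the printed imaging thresholds do not fit the two-network design. The firmest part needs no assumption about r. DMN–SN connectivity is one comparison, so its threshold is 0.05 and not 0.031, and the FPN threshold has nothing in the design to apply to.

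For the subnetwork graph measures, the printed 0.026–0.027 is stricter than the plan's rule if the family is the two networks within a measure (0.033–0.034). It is looser if the family is the five measures within a network (about 0.020). Both figures assume that the quoted correlations apply. Because the text promises one threshold per measure and prints one per network, the direction cannot be settled from the document.

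This should be fixed, but it does not threaten the main result. Only the secondary imaging outcomes are affected, and the YGTSS analysis is untouched.

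**What to change.** Revise the correction paragraph in Statistical analysis as follows.

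1. Delete FPN and the four fixed pairs of correlation and threshold.
2. State that DMN–SN connectivity is tested once at 0.05.
3. State the graph-measure family and its K for the DMN and SN: the two networks within each measure, or the measures within each network. Make the wording and the number of thresholds agree.
4. If a correlation enters a threshold, give the rule and not a number. Estimate r from this trial's baseline scans, pooled over arms, before after-training data are opened.
5. If FPN is intended, define it, add its ROIs under Construction of the network, and count it throughout, including three between-network pairs.

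The cost is the rewording of one paragraph, plus the ROI text if FPN is kept. The thresholds will change. DMN–SN connectivity gets a looser one, and the graph measures may get a stricter one, depending on the family stated and the correlation found.

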### Clinical trial registry

The study is a double-blind RCT reviewed and approved by the Ethics Committee of Beijing Children's Hospital, Capital Medical University. All participants and their guardians will provide their informed consent and sign the informed consent form. If the study participants feel unwell, they can withdraw from the study at any time and have a follow-up doctor for further examination and treatment. The trial is registered on the Chinese Clinical Trial Registry (ChiCTR2100053077, http://www.chictr.org.cn).

## Discussion

This protocol describes a study assessing the efficacy of MHRT for children with TS and associated brain network mechanisms. To the best of our knowledge, this is an original intervention technology that may be valuable for the non-drug treatment of TS. The protocol was designed to investigate multiple aspects of the treatment response, not only tic severity but also the effects of MHRT, HRT and PST on psychosocial functioning and neural physiological mechanisms.

Our results may be consistent with previous studies in patients with TS that compared the effectiveness of HRT and PST in a similarly large sample of TS patients. Based on available pilot data, we predict that patients receiving MHRT or HRT may show significant and clinically meaningful reductions in tic severity compared with patients receiving PST. We speculate that augmenting HRT with mindfulness training will enhance tic severity reductions and result in stronger awareness and lower anxiety levels. The fMRI scans may show functional changes in brain networks associated with mindfulness.

Mindfulness training can improve performance in attention, working memory and cognitive control tasks (55–57). With the potential benefits of mindfulness in children with common neurodevelopmental disorders (58), more research has been conducted in recent years. In 2020, a study investigated the feasibility of a family-based mindfulness intervention in 100 attention-deficit/hyperactivity disorder (ADHD) children's families and found that the intervention group showed greater improvements in children's ADHD symptoms (59). In 2021, Muratori et al. in a 50-child sample of adolescents with ADHD and oppositional defiant disorders showed that participating in a mindfulness meditation was associated with a greater reduction in hyperactive behaviors in the school context (60). Another pilot study using mindfulness training for children aged 8–12 years with ADHD (*n* = 140) and their parents also showed promising results (61). A study in Hong Kong demonstrated the feasibility of a mindfulness program in the Chinese context (62). Accumulating evidence supports the applicability of mindfulness-based therapy for those with mental health and neurodevelopmental disorders. The theoretical basis suggests that it can also be beneficial for patients with TS.

The mechanisms underlying mindfulness mainly involve two brain networks: the DMN and SN (26, 63, 64). The insula and anterior cingulate, which are responsible for premonitory impulses, are the key nodes in the SN network, and this network is dysfunctional in those with TS (31, 32, 65). Research shows that the main function of this network is to screen internal and external “key stimuli” (22, 63). We speculate that with the integration of mindfulness training technology, the first improvement with MHRT is enhancing the brain functional connections of the network such that the neural signals of PUs can be more easily “screened”. The default network is more closely related to “self”-related processing, and mindfulness training can improve an individual's self-awareness (66). Therefore, improved brain function involving the default network may improve the ability to detect PUs. In addition, the relief provided by mindfulness for the emotions associated with anxiety will also contribute to the awareness of PUs.

We need to be aware of the importance of HRT and spur further development. Psychological studies have argued that the learned associations acquired in HRT disrupt the negative reinforcement cycle that maintains tic expression (67–70). A large amount of evidence-based medical evidence confirms the effectiveness of this process. However, as a treatment response is associated with a 25–35% reduction in tic severity (71), there is room for improvement in therapeutic outcomes. In addition, few hospitals have performed such therapy, and no efforts have been dedicated to the study and development of the corresponding therapy plan in China. Exploring the biological mechanism and selecting the synergistic therapeutic mode based on the mechanisms, appropriately simplifying treatment sessions, developing group and network therapy, and strengthening the cultivation of professional personnel can make this therapeutic service more effective. Therefore, we emphasize the urgency of the development of this therapy in China. This protocol provides practical clinical significance and value given the current situation. MHRT can play a synergistic role based on HRT, but its efficacy evaluation and elucidation of brain mechanisms have important implications. Through this RCT, we can determine how to best evaluate the most important link between HRT and MHRT interventions and PUs. From a more objective perspective of the brain network, we will clarify the synergistic mechanisms underlying the effects of MHRT. This can provide a more practical and effective psychological intervention for children with TS to train and practice.

